**Discussion:**

The results of this trial will provide information on the safety and effectiveness of yoga for women with secondary arm lymphoedema from breast cancer treatment. It will also inform methodology for future, larger trials.

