## Methods/design

### Study design and setting

This study is designed to be a randomised controlled trial for women with stage one BCRL, as defined by the International Society of Lymphology [16]. The study will compare the results of a group who receive an integrated yoga intervention, to a control group who will continue to follow current best-practice in self-management of lymphoedema from a manual given to all participants pre-randomisation, but who will receive no yoga intervention. The control group will be wait-listed for the yoga intervention and so will be invited to participate at the completion of the study.

Measurements will be conducted at baseline (week 0), after which participants will be randomised to the yoga intervention or the control group. Further measurements will be made at week 4 (mid-point), week 8 (on completion of the yoga) and at week 12 (four weeks after the intervention).

The trial will be held at two locations, Hobart and Launceston. Both locations will consist of an intervention and control group. The study will be conducted at Community Health Centres in both locations.

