### Ethical considerations

The study has been approved by the University of Tasmania Social Sciences Ethics committee. Yearly progress reports will be made to the ethics committee and they will be notified of any adverse events promptly. The trial has been registered with the Australian New Zealand Clinical Trials Registry (ACTRN12611000202965, http://www.anzctr.org.au/default.aspx).

All women in the trial will receive information in a manual specifically developed for this trial on best current practice for management of secondary lymphoedema, based on the guidelines of the Australasian Lymphology Association and Lymphoedema Framework [16,39].

Women will be advised to continue with their usual treatment plan during the trial and to seek medical help in the case of infection or a flare-up of lymphoedema. Should this occur, women will be advised they can continue with the trial but told their measurements will not be included in the results, as it will change their status with regard to the eligibility criteria.

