### Sample size calculation

An *a priori* sample size calculation based on clinically significant changes between groups of between 10-20% in primary outcome measures with standard deviations of between 12 and 15% of the mean, or within groups 10% difference with an SD of 20%, indicated that numbers of between 13 and 19 participants would be required per group. Consequently, we plan on recruiting 20 participants per group to allow for a small number of withdrawals.

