### Data analysis

Medical and demographic information will be analysed using descriptive analysis within SPSS (version 19SPSS Inc. IBM, USA 2010) to calculate means and standard deviations or percentage values. Differences between groups will be assessed using t-tests for comparing continuous variables and chi-square tests for categorical variables.

All statistical analyses for quantitative measurements will be performed using STATA statistical software (version 12; 1985-2011; STATA corp.; College Station; Texas, USA). Binary categorical data will be analysed for variability between the groups using logistic regression. Parametric longitudinal data will be analysed via mixed methods linear regression. Non-parametric data will use ordinal logistic regression. Post-hoc testing will be performed on both parametric and non-parametric data using the Holms test to locate the means that are significantly different. Statistical significance will be set at p < 0.05.

Qualitative data from interviews will be analysed using an iterative-thematic approach.

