## Discussion and conclusion

The aim of this trial is to determine the effect of a yoga intervention on women with secondary arm lymphoedema as a result of breast cancer treatment by comparing the measurements of the intervention group with those of the control group, as well as to assess the perceived effects of yoga on the women in the intervention group by interview.

As no such trial has occurred up to this time, the results will assist in determining the effects of yoga on aspects relating to the lymphoedema, quality of life and upper body functioning for women with BCRL in the hope of finding another safe self-care option for women with BCRL. Finally, the methodology will inform future studies with larger numbers, as well as teaching guidelines for use by qualified yoga teachers.

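### The stated 13 to 19 women per group matches a between-arm difference of about 14%, not the 10% end of the range it is said to cover, and the within-group alternative does not size the yoga-versus-control comparison

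*Protocol article*

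**What the plan says.** The Sample size calculation section of the protocol article offers two bases for one number. The first is "clinically significant changes between groups of between 10-20% in primary outcome measures with standard deviations of between 12 and 15% of the mean". The second follows in the same sentence: "or within groups 10% difference with an SD of 20%, indicated that numbers of between 13 and 19 participants would be required per group". From this, "we plan on recruiting 20 participants per group to allow for a small number of withdrawals".

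The comparison of interest is stated twice as between arms. Under Study design and setting: "The study will compare the results of a group who receive an integrated yoga intervention, to a control group". Under Discussion and conclusion, the aim is to be met by "comparing the measurements of the intervention group with those of the control group".

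Under Data analysis, "Statistical significance will be set at p < 0.05". Neither power nor sidedness is given. That section also plans mixed linear regression for the longitudinal parametric outcomes, which are measured at weeks 0, 4, 8 and 12.

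Two statements bear on how many women will be analysed. The sample size section expects some withdrawals. Ethical considerations says of women with an infection or flare-up that "their measurements will not be included in the results".

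**The concern.** There are two difficulties. First, the section calls differences from 10% upwards clinically significant and gives 13 to 19 per group as the requirement. A reader would take that number to serve the whole 10-20% range, but a simple two-group calculation gives a larger number at the 10% end. Second, the section accepts a within-group change as an alternative route to the same number. A within-group test has no control-arm variance to carry, so a number that suffices for it does not suffice for a between-arm difference of the same size.

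What is at stake is how a null result is read. If a benefit that the protocol itself regards as clinically significant is fairly likely to be missed, a non-significant comparison says little about it. The abstract also says of the trial: "It will also inform methodology for future, larger trials". An unqualified 13 to 19 is the kind of figure a later planner may carry forward.

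**Working it through.** **Inputs.** From the sample size section: between-group difference 10-20%; SD 12-15% of the mean; within-group difference 10% with SD 20%; stated need 13 to 19; planned 20 per group. From Data analysis: significance level 0.05. Assumed: two-sided test, 80% power.

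**1. Between-group inputs, one time point, no adjustment.** The normal approximation is n = 2(1.960 + 0.842)² × (SD/difference)² per group, which at 10% gives 22.6 (SD 12%) and 35.3 (SD 15%). The exact two-sample t-test gives slightly more:

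| Difference | SD 12% | SD 15% |
|---|---|---|
| 10% | 23.6 → 24 | 36.3 → 37 |
| 14% | 12.6 → 13 | 19.03, about 19 |
| 15% | 11.1 → 12 | 16.7 → 17 |
| 20% | 6.8 → 7 | 9.9 → 10 |

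The full span is 7 to 37. The plan's 13 to 19 is reproduced at a difference of 14% (19 per group gives 79.9% power at SD 15%).

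Other assumptions: 90% power at 10% needs 32 to 49; a one-sided test at 80% power needs 19 to 29.

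**2. Power, same unadjusted comparison.**

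| Per group | 10%, SD 12% | 10%, SD 15% | 15%, SD 12% | 15%, SD 15% |
|---|---|---|---|---|
| 20 | 73% | 54% | 97% | 87% |
| 19 | 71% | 52% | 96% | 85% |
| 18 | 68% | 49% | 95% | 83% |
| 13 | 53% | 37% | 86% | 69% |

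These figures need two-sidedness and the stated 0.05, but not the assumed 80%.

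**3. What 20 per group detects.** With 80% power the detectable standardised difference is 0.909. That is 0.909 × 12 = 10.9% and 0.909 × 15 = 13.6%. The 95% interval half-width is 2.024 × SD × √(2/20), which is 7.7 and 9.6 percentage points. With 18 per group the detectable differences rise to 11.5% and 14.4%.

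**4. Within-group clause.** If 20% is the SD of change, a one-sample t-test of 10% (standardised change 0.5) needs 33.4 → 34 women, and 19 women give 54% power. If 20% is instead the raw SD, the SD of change is 20 × √(2(1 − r)), where r is the correlation between visits. At r = 0.73 this is 14.7 and n is 19; at r = 0.70 it is 15.5 and n is 21. The section gives no r.

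Either way the result does not transfer to two arms. If 19 women give 80% power for a within-group change, the standardised change is 0.680. A between-arm difference in change of that size has 53% power with 19 per arm and needs 35 per arm.

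**5. Gains that could bring 10% within reach.**

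- *Baseline adjustment, one follow-up.* SD becomes SD × √(1 − r²). For 10% at 80% power this needs 18 to 28 per group at r = 0.5, 16 to 24 at r = 0.6, and 13 to 20 at r = 0.7 (unrounded 12.6 and 19.02).
- *Averaging m follow-ups, baseline-adjusted.* With equal correlation r between all visits and the same effect at each, the variance is multiplied by (1 + (m − 1)r)/m − r². For m = 2 and r = 0.5 this is 0.75 − 0.25 = 0.50, giving 12.3 to 18.7 per group. The factor peaks at 0.5625 (r = 0.25), giving 13.8 to 20.9. For m = 3 the need is at most about 11 to 17. With 20 per group and m = 2, power at 10% is at least about 93% (SD 12%) or 78% (SD 15%).

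**The case against.** The best defence has four parts.

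*The stated number lies inside the span of its inputs.* This stands. A range of differences and a range of SDs were given, and an ordinary two-group calculation at 14% returns 13 and 19. A reader might infer that the inputs flatly contradict the number, or that the protocol says 13 to 19 is enough for 10%; it says neither. A one-sample formula applied to 10% with SDs of 12% and 15% gives 13.35 and 19.67, which truncate to the same pair. It is tempting to conclude that the wrong formula was used, but since the 14% calculation fits as well, the text cannot show which was done.

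*The planned analysis is a mixed model over several visits.* This stands in part. The 54% to 73% describes one unadjusted time point and is not the power of the trial under every analysis. Nor is a correlation near 0.7 the only way to recover the stated range, since averaging two follow-ups can do so at any non-negative correlation, to within about two women. However, that needs the same effect at each visit. Week 4 is mid-intervention and week 12 is four weeks after it ends, so a constant effect is doubtful, and the sample size section does not invoke it.

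*Power, sidedness and correlation may be in the full protocol.* Agreed, and their absence from an article is not the complaint. The complaint is that the printed range of differences and the printed number do not match on a plain reading.

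*It is a pilot.* The abstract says so, and a pilot may be small. But the section presents a calculated requirement, and the Background states efficacy hypotheses.

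**Conclusion.** The point holds in a limited form. On an unadjusted two-sample test at two-sided 5% and an assumed 80% power, 13 to 19 per group serves a difference of about 14%. The 10% difference that the protocol calls clinically significant needs 24 to 37, and has 73% to 54% power with 20 per group. At 15-20%, 20 per group is adequate (87% power or more). The 10% end is reached across the stated SDs only by a baseline correlation near 0.7, by averaging visits under a constant effect, or by some similar gain that the section does not state.

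The within-group clause is the clearer fault: it does not size the comparison the trial is built to make, whatever SD is meant.

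A reader might conclude that the trial must recruit 24 to 37 per group. The documents do not support that. The shortfall depends on the analysis assumed, and a pilot of 40 women is defensible once it states what it can detect.

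**What to change.** Keep 40 women and rewrite the sample size section:

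- Delete the within-group clause and rest the number on the between-arm difference alone.
- State that 20 per group detects a between-arm difference of about 11% (SD 12%) to 14% (SD 15%) with 80% power in an unadjusted comparison at one time point, with a 95% interval of about ±8 to 10 percentage points. Add that the detectable difference grows with withdrawals and exclusions, for example to 11.5% to 14.4% at 18 per group.
- If the 10% target relied on baseline adjustment or repeated measures, state that assumption, its source and the resulting number instead.
- Report within-arm changes as descriptive, and say that a null between-arm result does not exclude a 10% benefit.

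The cost is a few sentences and no extra participants. The downside is a less favourable stated detectable difference. Recruiting 24 to 37 per group would add (24 − 20) × 2 = 8 to (37 − 20) × 2 = 34 women before any allowance for loss. With a two-month recruitment period in one state, that is not a cheap remedy and is not recommended here.

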**Methods and design:**

A randomised controlled pilot trial will be conducted in Hobart and Launceston with a total of 40 women receiving either yoga intervention or current best practice care. Intervention will consist of eight weeks of a weekly teacher-led yoga class with a home-based daily yoga practice delivered by DVD. Primary outcome measures will be the effects of yoga on lymphoedema and its associated symptoms and quality of life. Secondary outcome measures will be range of motion of the arm and thoracic spine, shoulder strength, and weekly and daily physical activity. Primary and secondary outcomes will be measured at baseline, weeks four, eight and a four week follow up at week twelve. Range of motion of the spine, in a self-nominated group, will be measured at baseline, weeks eight and twelve. A further outcome will be the women’s perceptions of the yoga collected by interview at week eight.

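### The stated requirement of 13 to 19 women per group does not follow from the differences and SDs given for it

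*Protocol article*

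**What the plan says.** The Sample size calculation section gives two alternative bases. The first is "clinically significant changes between groups of between 10-20% in primary outcome measures with standard deviations of between 12 and 15% of the mean". The second is "within groups 10% difference with an SD of 20" per cent. From these it concludes that the calculation "indicated that numbers of between 13 and 19 participants would be required per group", and then: "we plan on recruiting 20 participants per group to allow for a small number of withdrawals". The Abstract gives the same total, "with a total of 40 women receiving either yoga intervention or current best practice care", so allocation is 1:1.

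The section names no test, power, sidedness, baseline correlation or withdrawal rate. Alpha appears only under Data analysis: "Statistical significance will be set at p < 0.05".

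**The concern.** The sentence prints both its inputs and its result, so a reader can check one against the other. The inputs are wide: the difference varies by a factor of two and the SD by a factor of 1.25. The result is narrow. A narrow range of sample sizes cannot come from such wide inputs under one test and one power.

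The justification of the trial size is at stake. A reader is told that 19 women per group suffice for every effect in the range called clinically significant, including the 10% end. If they do not, a non-significant result at that end says less than the protocol implies, and a later trial that takes over the calculation inherits the error.

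**Working it through.** **Inputs.** From Sample size calculation: differences of 10% and 20%; SDs of 12% and 15%; within-group 10% with SD 20%. From Data analysis: alpha 0.05. From the Abstract: 1:1 allocation.

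**Assumptions, because the document is silent.** Two-sided test, 80% power (90% and one-sided also tried), no baseline adjustment, differences and SDs as percentages of the same mean, and the within-group 20% taken as the SD of the change.

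**Step 1: a check that needs no power.** For two means, n per group ≈ 2(z₁₋α/₂ + z₁₋β)² × (SD/difference)². Alpha and power enter only through the first factor, which cancels when two cases are compared:
- Largest case, 10% with SD 15%: (15/10)² = 2.25.
- Smallest case, 20% with SD 12%: (12/20)² = 0.36.
- Ratio: 2.25/0.36 = 6.25. With the exact t-test at 80% power it is 36.3/6.76 = 5.4.
- Stated range: 19/13 = 1.46.

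No single alpha, power or sidedness closes that gap.

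**Step 2: required n per group.** Worked example by the normal approximation at 80% power, for 10% with SD 12%: 2 × (1.960 + 0.842)² × (12/10)² = 2 × 7.849 × 1.44 = 22.6. The noncentral t gives 23.6, so 24. All cases by the noncentral t, rounded up:

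| Case | Two-sided, 80% | Two-sided, 90% | One-sided, 80% |
|---|---|---|---|
| 10%, SD 12% | 24 | 32 | 19 |
| 10%, SD 15% | 37 | 49 | 29 |
| 20%, SD 12% | 7 | 9 | 6 |
| 20%, SD 15% | 10 | 13 | 8 |
| Within-group 10%, SD 20% (paired) | 34 | 44 | 27 |

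The between-group range is 7 to 37, 9 to 49 or 6 to 29. In the first column no case falls within 13 to 19. In each of the other two columns a single case touches an end of that range.

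**Step 3: attempts to reproduce 13 to 19.** Three calculations come close:
- A one-sample or paired t-test of 10% with SD 12% and 15% at 80% power gives 13.35 and 19.67. This is not a between-group calculation.
- The two-sample test of 10% gives 13 and 19 per group, but at 50% power.
- The two-sample test of 20% at 80% power gives 13.5 and 19.8 as the total for both groups, not per group.

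None matches the sentence as written.

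**Step 4: what 20 per group gives (unadjusted, two-sided 5%).** The detectable difference at 80% power is 0.909 SD with 20 per group and 0.934 SD with 19:
- SD 12%: 0.909 × 12 = 10.9% with 20; 0.934 × 12 = 11.2% with 19.
- SD 15%: 0.909 × 15 = 13.6% with 20; 0.934 × 15 = 14.0% with 19.

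Power for a 10% difference with 20 per group is 73% at SD 12% and 54% at SD 15%. Power for the within-group case is 54% with 19 women and 56% with 20.

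**The case against.** The strongest defence is that the planned analysis is more efficient than an unadjusted t-test. The trial measures women at baseline and three later times, and Data analysis plans a mixed linear regression. Suppose, as an assumption, that the baseline correlation is 0.7 and the analysis adjusts for baseline. The SD then shrinks by √(1 − 0.7²) = 0.714, and the 10% cases need 12.6 and 19.0 per group at two-sided 5% and 80% power, close to the stated pair. Power with 20 per group would be 95% and 82%; at a correlation of 0.6 it would be 89% and 73%. Similarly, if the within-group 20% is a raw SD and the correlation is 0.75, the paired case needs 18.

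This shows that the stated numbers could be adequate under assumptions that are not printed. It does not rescue the sentence. No correlation is given, and at 0.7 the 20% cases would need only about 4 to 6, so the range still does not match. Interior pairings, such as 15% with SD 15% (17 per group), do fall inside 13 to 19, but the text claims the whole 10 to 20% range.

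It can also be said that this is a pilot trial and that a journal article condenses. Omitting power and sidedness is fair in an article and is not the complaint. The complaint is that the printed inputs and the printed result are incompatible at any one setting. Pilot status limits the consequences but does not make the figure right.

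**Conclusion.** The statement that 13 to 19 women per group are required is wrong as written. That conclusion rests on the scaling in step 1 and does not depend on the missing power. The sizes (7 to 37 per group between groups, 34 within group, 54 to 73% power for a 10% difference) rest on an unadjusted two-sided 5% comparison, and the required numbers also on 80% power.

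Four stronger readings might be inferred and are not supported:
- *That 20 per group can never reach a 10% difference.* The hypothesis in the Background is directional and sidedness is not stated. With a one-sided 5% test and SD 12%, 18.5 per group suffice for 80% power, and 20 give 83%. At SD 15% the one-sided power is about 66%.
- *That the trial as it will be analysed has only 54 to 73% power.* The planned longitudinal model could do better, by an amount the document does not allow one to compute.
- *That the authors used a one-sample formula by mistake.* The near match in step 3 is suggestive, but nothing in the text confirms it.
- *That the withdrawal margin or the several primary outcomes add to the arithmetic error.* The margin of 20 covers one loss per group against 19 but seven against 13, and the text claims only a small allowance. Multiplicity is a separate question, and its detail may lie in a plan that is not shown.

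**What to change.** Rewrite the Sample size calculation paragraph:

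1. Keep 20 per group and withdraw the 13 to 19 requirement.
2. Do not use the within-group case (10%, SD 20%) as support. It has about 54 to 56% power at 19 to 20 women, and the trial compares yoga with control.
3. State the test, sidedness, power and any baseline correlation, and give the matching detectable difference. For an unadjusted two-sided 5% comparison at 80% power, suitable wording would be: with 20 women per group (19 completing), the trial can detect a between-group difference of about 0.91 SD (0.93 SD), that is, about 11% of the mean if the SD is 12% and 14% if it is 15%; power for a 10% difference with 20 per group is about 73% and 54% respectively.
4. If a baseline-adjusted analysis or a one-sided test is intended, say so, give the assumed correlation and its source, and recompute the figures on that basis.

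The cost is one rewritten paragraph and a less favourable stated figure. No extra women are needed, and neither the design nor the analysis changes.

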### Participants

Eligibility criteria based on previous exercise trials for women with BCRL will be followed [26,40]. Criteria for inclusion are completion of treatment for breast cancer in terms of surgery, radiotherapy and chemotherapy at least 6 months previously; unilateral secondary lymphoedema stage one related to surgery for breast cancer, as confirmed by a registered lymphoedema therapist; good English comprehension in order to understand the written forms and oral instructions and be able to give informed consent; aged > 18 years.

Criteria for exclusion are conditions of primary lymphoedema, recurrent cancer and other symptoms including infection or cellulitis, which would affect the woman’s lymphoedema and her quality of life adversely; severe psychological illness, as the yoga intervention would need to be specific to the person’s psychological illness in order to improve it; pregnant women and women with pacemakers, as these conditions are contra-indicated for the use of bio-impedance spectroscopy – one of the measuring tools for this study [41]; current lymphoedema treatment other than self-management, as this would affect the results.

Women will also be asked to refrain from commencing any new physical activity during the term of the trial as this could affect results.

